**Figure 1 figure1:**
[figure not shown]
CONSORT (Consolidated Standards of Reporting Trials) diagram of the Recovery ACT Trial. ACT: Acceptance and Commitment Therapy.

**Table 1 table1:** World Health Organization Trial registration data set.

Data category		Information
Primary registry and trial identifying number		ANZCTR, ACTRN12620000223932
Date of registration in primary registry		February 24, 2020
Secondary identifying numbers		UTN: U1111-1247-8144
Source of monetary or material support		Royal Melbourne Hospital, NorthWestern Mental Health
Primary sponsor		Royal Melbourne Hospital, NorthWestern Mental Health
Secondary sponsor		La Trobe University
Contact for public enquiries		[name]
Contact for scientific enquiries		[name]
Public title		Acceptance and Commitment Therapy (ACT) Group Program for Recovery from Psychosis: A Multi-Agency Evaluation
Scientific title		A Multi-agency Evaluation of the Routine Practice of an Acceptance and Commitment Therapy Group for Recovery from Psychosis
Countries of recruitment		Australia
Heath conditions or problems studied		Psychosis, Mental Health, Schizophrenia
Interventions		Treatment: “Recovery ACT for Psychosis” Group Program; comparator or control: single group, waitlist control period
**Key inclusion and exclusion criteria**		
	Inclusion criteria	Inclusion criteria: Out-patients aged between 18 and 65 years; have a primary file diagnosis of either a schizophrenia spectrum or other psychotic disorder, a mood disorder with psychotic features, or a substance-induced psychotic disorder; are currently receiving outpatient mental health care at one of the study centers; are self-referred or referred by clinical staff to a Recovery ACT group being conducted by a participating center.
	Exclusion criteria	Exclusion criteria: lack of capacity to consent to this evaluation; lack of proficiency in speaking and comprehending English; file diagnosis of an intellectual disability (an intellectual development disorder) or borderline personality disorder.
Study type		Interventional
Allocation		Nonrandomized trial Intervention assignment: single-group Masking: open (masking not used)
Primary purpose		Treatment
Phase		N/A^a^
Date of first enrollment		September 13, 2019
Target sample size		160
Recruitment status		Recruiting
Primary outcomes		Personal recovery
Key secondary outcomes		Well-being

^a^N/A: not applicable.

### Procedure

#### Recruitment

Participants will be recruited from current consumers of the services enrolled in a Recovery ACT group program as part of their normal clinical care. Recovery ACT group programs are conducted at all 4 participating sites, either as part of a program of groups offered to consumers or as periodic opportunities. All sites follow the same recruitment plan. Recruitment will continue until the target is met, as long as the clinical services are willing to continue to support the evaluation. Facilitators will describe the group program and the evaluation study at staff meetings and with fellow clinicians at their study site to ensure they are aware that an evaluation of the program is occurring and that consumers will be invited but not obligated to participate. Facilitators will receive all referrals to the group program and contact potential consumers to schedule an “Information and Engagement” session to brief consumers about the group program and confirm their wish to attend. All consumers who enroll in the group program will be screened for eligibility to participate in the evaluation. Consumers who meet the eligibility criteria will be provided with an explanation of the study, an information sheet, and an evaluation brochure, and those who choose to participate will be required to provide written informed consent.

After the completion of a group program (after the booster session), senior investigators will invite facilitators to participate in a semistructured group interview for evaluation purposes and seek informed consent.

Due to the time elapsed from the initial consent process, all group members will be asked again at either session 7 or the booster session for permission and written consent to contact them in the future to invite them to participate in a follow-up study on the experience of participating in the group.

#### Intervention

The Recovery ACT group program includes 7 core sessions scheduled weekly and a booster session scheduled approximately 4 weeks later. The duration of all sessions is 90 minutes, and they are delivered in person. The intervention is an adaptation of the ACT for Life program [30] that centers on a core metaphor (passengers on the bus) [38] to facilitate consumers’ engagement in value-based actions when relating to their internal experiences (eg, thoughts, feelings, and memories) once they become aware of the internal experiences and are able to defuse (or cognitive distance) from them. The group focuses on developing awareness of internal experiences through metaphors and mindfulness activities and building defusion skills. In the metaphor, the “bus” represents the consumer’s life in the present moment, the “bus driver” is the consumer, and the “passengers” on the bus are the consumer’s internal experiences. The topics covered during the core sessions include: introduction to noticing (mindfulness) of present experiences and values; enacting the core passengers on the bus metaphor and “specific, meaningful, adaptive, realistic, and time-framed” (SMART) goals; review of values, noticing, and willingness; identification of passengers and different ways of responding to them and development of noticing skills; passengers on the bus and changing relationships with words; review of values and encouragement of sharing value-guided actions; and review of key group messages. Brief contact with consumers between sessions is encouraged to promote completion of home practice and to encourage attendance.

There are no specified criteria for discontinuing or modifying the intervention, as this is an evaluation of a group program as conducted in routine clinical practice at local mental health services. Participants can choose to withdraw from the evaluation and remain in the group program. Participants may be withdrawn from the study due to a protocol violation or an adverse event.

Facilitators will be clinical mental health staff employed at a participating public mental health service who, where possible, have participated in an introductory ACT workshop and completed training in Recovery ACT. The group is led by 2 facilitators, one of whom is experienced (ie, has previously led a Recovery ACT group program) and adheres to the Recovery ACT group program manual [39]. Facilitators will be invited to attend a minimum of 3 “Support and Supervision” sessions while facilitating a group. The goal of these sessions is to enhance fidelity to the Recovery ACT group program manual [39]. In addition, facilitators will complete a fidelity log after each group session.

There are no restrictions on concomitant care and interventions, as this is an unfunded evaluation of the Recovery ACT group program that is already offered in routine clinical care at the participating public mental health services. To participate in the Recovery ACT program, participants must be receiving care at the respective public mental health service. As such, participants will receive provisions for ancillary and posttrial care at the public mental health service. The potential risks related to the study are deemed minimal. Facilitators are responsible for participants’ clinical care during the group program, including distress related to study procedures. Participants have a key support clinician for out-of-group issues that may arise.

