### Objectives

The primary aim is to evaluate the effectiveness of the Recovery ACT group program on personal recovery for adults living with a psychotic disorder in routine clinical practice across public mental health organizations in Australia using a single-group, waitlist control design. A secondary aim is to evaluate the effect of the Recovery ACT group program on well-being and psychological flexibility processes (experiential avoidance, cognitive defusion, engagement in valued actions, and mindfulness). The research questions are as follows: (1) What are the clinical benefits and risks of the Recovery ACT group program for adults diagnosed with psychotic disorders as conducted in routine practice in Australia? (2) Are there changes in psychological flexibility processes due to participation in the Recovery ACT group program? (3) Are changes in psychological flexibility processes associated with changes in personal recovery and well-being?

The primary and secondary hypotheses are that the longitudinal trajectory of personal recovery and the secondary outcomes will not significantly change over the waitlist period, then will improve from the start to the end of the group program, and then improve at a less rapid rate from the end of the group to the booster session. A further hypothesis is that changes in psychological flexibility processes during the first half of the group program will be associated with changes in personal recovery and well-being in the second half of the group program.

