### Statistical Methods and Sample Size

We intend to use an intention-to-treat sample to test a univariate latent growth curve model of the primary outcome from before the start of the waitlist period to the start of the group to the booster session in order to compare the trajectory over the waitlist period to the trajectory over the active treatment period. We selected this method of analysis to strengthen our estimations of associations due to the limitations of the nonrandomized study design chosen as the most realistic option for an evaluation of a program already in routine practice [51]. A minimum sample size of 90 is required to conduct the proposed growth curve structural equation model (5 observed variables and 2 latent variables) with an anticipated medium effect size (0.3), α set at .05, and power (1–β) at .80. Univariate latent growth curve models for each of the 5 secondary outcomes will also be tested. If there are sufficient data, we will test whether the trajectory of the 4 psychological flexibility process variables from the start of the group to the midpoint session (T1 to T2) is significantly associated with the trajectory of personal recovery (T2 to T4) using multivariate growth models. We do not predict a priori any differences associated with the study site. We intend to calculate the ICC after the data are collected to determine the relatedness of the data collected at different study sites.

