#### Data Collection and Management

The data will be collected using deidentified hardcopies of all evaluation documents (quantitative questionnaires completed by participants and facilitators, copies of qualitative feedback forms, and demographic and clinical information forms), and other trial documents (attendance records, fidelity logs, and recruitment logs). Facilitators will assist participants with questionnaire completion if needed. As facilitators will serve a dual role as clinical service providers and study personnel, participants will be provided a sealable envelope to return deidentified self-report questionnaires that will be reviewed by study personnel other than their facilitators if sealed (either at the site or by the study coordinator). If a participant does not attend a group session when data are collected, facilitators will attempt to schedule an appointment to complete study measures.

Deidentified data from hard copy evaluation documents will be entered into a password-protected electronic file maintained on secure computers by the study coordinator. A coding sheet with identifiable participant information will be saved as a password-protected electronic file on the sponsor site’s server. Hard copies of consent forms and study documents will be kept in a locked filing cabinet at the Academic Psychology Unit located at the sponsor’s site.

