#### Data Monitoring and Adverse Event Reporting

Anticipated risks to participant safety due to participation in the evaluation and the group are deemed minimal based on pilot study data [35]. Therefore, there is no data monitoring committee, and there are no planned interim analyses to identify risks. Adverse events will be monitored by facilitators, site principal investigators, the coordinating principal investigator, and the Interagency Investigator Committee. An adverse event form and guideline are used.

An Interagency Investigator Committee led by the coordinating principal investigator meets quarterly to oversee the trial’s progress, monitor any adverse events or serious adverse events related to the procedures or the group program, and discuss any necessary protocol modifications. A study coordinator is responsible for liaising with the site principal investigators, who are responsible for the evaluation at each site. In addition to the published Recovery ACT group program manual, evaluation procedure manuals were created to ensure that the protocol is adhered to by study personnel at all sites and over the course of the multiyear study.

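### The rule allowing withdrawal from the study for an adverse event or protocol violation can end outcome collection for outcome-related reasons and is not reconciled with the intention-to-treat sample or the question about risks

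*Protocol article*

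**What the plan says.** Three statements in the Intervention section belong together. On the program itself: "There are no specified criteria for discontinuing or modifying the intervention". On the participant's own choice: "Participants can choose to withdraw from the evaluation and remain in the group program". On withdrawal decided by others: "Participants may be withdrawn from the study due to a protocol violation or an adverse event". The second statement makes the evaluation something a person can leave while staying in the group.

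Under Statistical Methods and Sample Size the authors write: "We intend to use an intention-to-treat sample to test a univariate latent growth curve model of the primary outcome". The first research question, under Objectives, begins: "What are the clinical benefits and risks of the Recovery ACT group program". Randomization and Blinding explains that each participant is their own control, with change over the waitlist compared with change during the program.

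Two further passages bear on follow-up. Data Collection and Management says: "If a participant does not attend a group session when data are collected, facilitators will attempt to schedule an appointment to complete study measures". Data Monitoring and Adverse Event Reporting says: "Adverse events will be monitored by facilitators, site principal investigators, the coordinating principal investigator, and the Interagency Investigator Committee".

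**The concern.** An adverse event or a protocol violation after enrollment is something an intention-to-treat approach is normally meant to keep in view. A rule that allows the evaluation to end for that person means that T3 and T4 scores may never be collected, for a reason that may be linked to how the person was doing. A later analysis plan can say how missing scores are modeled, but it cannot recover scores that were not sought.

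This design is exposed in a particular way. A person withdrawn between T1 and T3 leaves T0 and T1 in the data, so the waitlist segment is complete while the treatment segment loses its end-of-group and booster scores. There is no second arm in which a similar selection could partly cancel. If those withdrawn after an adverse event did worse than their earlier scores suggest, the estimated improvement would be too large, and the answer to the question about risks would lack their later outcomes.

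**Working it through.** **1. What the rule applies to.** The paragraph sets no criteria for stopping the program, lets a person leave the evaluation but stay in the group, and then speaks of withdrawal from the study. Read in sequence, study means the evaluation, that is, data collection. The rule is permissive and gives no criteria for its use.

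**2. Which data are lost, by time of withdrawal.**
- Before T1: both segments are lost.
- Between T1 and T3: the waitlist segment (T0, T1) is kept. T3 and T4 are lost, with T2 kept only where a site collected it in time.
- Between T3 and T4: only T4 is lost.

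After T1, the loss is therefore always on the treatment side of the comparison.

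**3. The plan's own figures.** The stated minimum is 90, with effect size 0.3, α .05 and power .80.
- An exact two-sided one-sample (paired) t test with d = 0.3 needs n = 90 (power 0.804).
- The usual lower bound for a structural equation model with two latent variables gives 89.1, hence 90.

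The figure reproduces either way, so it does not show whether 0.3 is a standardized mean change. Below, 0.3 is used as a yardstick on the assumption that it is.

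Retention: 160 × 0.60 = 96, which is 6 above 90. If study withdrawals came on top of the anticipated 40% loss (assumed):
- 2 percentage points: 160 × 0.58 = 92.8
- 5 points: 160 × 0.55 = 88
- 10 points: 160 × 0.50 = 80

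If they are already within the 40%, these numbers do not change.

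**4. Illustrative bias.** Let w be the share withdrawn and g the gap in mean change, retained minus withdrawn. The mean over everyone is (1 − w) × retained mean + w × withdrawn mean. Analyzing only the retained therefore overstates the mean change by w × g. Neither w nor g is in the article; both are assumed.

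| w | g = 0.5 SD | g = 1.0 SD |
|---|---|---|
| 1% | 0.005 SD (1.7% of 0.3) | 0.010 SD (3.3%) |
| 2% | 0.010 SD (3.3%) | 0.020 SD (6.7%) |
| 5% | 0.025 SD (8.3%) | 0.050 SD (16.7%) |
| 10% | 0.050 SD (16.7%) | 0.100 SD (33.3%) |

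Two things pull these values down. A growth model that uses incomplete series removes the part of g that earlier scores predict. Also, some of those withdrawn would have been lost anyway, given 40% anticipated loss, so continued follow-up would recover less than the table suggests.

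**The case against.** A reader might infer that the rule contradicts intention-to-treat. The article does not support that. An intention-to-treat sample defines who is analyzed, and nothing says that withdrawn participants leave it or that their earlier scores are discarded. A latent growth model can use T0 and T1 from someone with no later data. Both statements can be followed together, although the result then depends on an assumption about the missing scores.

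A reader might also infer that follow-up is removed from the people most likely to have been harmed. That also goes too far. The rule says may, not must. Adverse event monitoring involves several parties, and nothing says that it stops at withdrawal; the event that prompts a withdrawal is already known and can count toward the risk question. A protocol violation need not involve harm; enrolling an ineligible person would be one. The article calls the risks minimal and describes the 90-consumer pilot as safe.

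It can further be said that the full protocol (version 8.0), the adverse event guideline and the procedure manuals may settle who decides and what follows. That is a fair reason not to fault the article for missing detail. It does not remove the point, because the article states a rule which, followed as written, permits T3 and T4 collection to end.

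Finally, a rule under which only withdrawn consent ends data collection would be too rigid. The article foresees distress caused by study procedures, and it excludes people who lack capacity to consent. This objection stands, and the fix makes room for both situations.

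**Conclusion.** The point holds as an unreconciled tension in a stated rule. Withdrawal from the evaluation for an adverse event or protocol violation allows outcome collection to end for reasons that may relate to outcome. After T1 the loss affects only the treatment segment. This sits badly with the intention-to-treat aim and weakens the answer on risks. No randomized comparison is broken, since there is one nonrandomized group; the problem is selective missingness in the within-person trajectory.

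The size cannot be fixed from the article. The range of 0.005 to 0.10 SD, about 2% to 33% of 0.3, rests on assumed shares of 1% to 10%, assumed gaps of 0.5 to 1.0 SD, analysis of the retained only, and 0.3 read as a standardized mean change. With risk described as minimal, the low end is plausible, and the upper end should not be cited as an expected bias. The direction, if withdrawn participants did worse, favors the program. The change is worth making because it is cheap and because uncollected scores cannot be restored.

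**What to change.** Amend the sentence in the Intervention section to say that an adverse event or protocol violation does not by itself end outcome collection. T3 and T4 measures continue to be sought through the appointment procedure already described under Data Collection and Management, unless the participant withdraws consent, loses capacity to consent, or the study procedures themselves cause the distress. Add under Statistical Methods and Sample Size that all data collected from these participants, including data from before any withdrawal, stay in the intention-to-treat analysis. Decisions about attending the group program are not touched.

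The cost is a short amendment and a few extra questionnaire appointments. It can still take effect: the article reports 93 consented toward a target of 160, enrollment open until at least 2024, and no analysis yet done.

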### Outcomes

#### Timeline

The schedule of enrollment, interventions, and assessments is displayed in Figure 2. The quantitative self-report outcome measures are intended to be completed independently at the start of the waitlist period (T0, approximately 4-6 weeks before the start of the group program, typically at the “Information and Engagement” session), at the start of the group program (T1), at the end of the group program (T3, which is 6 weeks after the start of the group program), and at the booster session (T4, about 10 weeks after the start of the group program). Some participants may complete outcome measures at the midpoint session (T2, which is 3 weeks after the start of the group program) if the study site is resourced to collect data at an additional time point. Measures are completed after the group session, except for at T1, when participants complete measures before the start of the group to ensure no exposure to the program’s content. Participants can request assistance from facilitators to complete the measures. Demographic and clinical information will be obtained from participants’ electronic health records at T0 and will include their date of birth, gender, ethnicity, country of birth, highest level of educational attainment, highest level of employment, current employment status, primary mental health file diagnosis, co-occurring mental health file diagnoses, date of first contact with mental health services, number of listed episodes of outpatient mental health care, and number of psychiatric admissions.

**Figure 2 figure2:**
[figure not shown]
Schedule of enrollment, interventions, and assessments.

#### Primary Outcome

The primary outcome is personal recovery, as measured by the 15-item version of the Questionnaire about the Process of Recovery (QPR) [40,41]. The 15-item QPR has good internal consistency (QPR total α=.89), fair to good test-retest reliability (QPR total intracluster correlation coefficient [ICC]=0.74), moderate sensitivity to change, and adequate convergent validity [42]. The QPR is a measure that assesses the 5 core processes of personal recovery that comprise the “Connectedness; Hope and optimism about the future; Identity; Meaning in life; and Empowerment” (CHIME) framework [43], which is currently the strongest conceptualization of personal recovery in serious mental illness. The Recovery ACT group program seeks to support change in these dimensions for participants.

